### User Experience

A total of 12 participants will be asked to participate in a qualitative research interview, focusing on the experience and acceptance of sleeping with the monitor nearby over an extended period. The number of informants for the qualitative research interviews is expected to be sufficient, as data saturation is typically achieved with 12 participants [41]. However, the final number of informants may vary slightly, depending on when data saturation is achieved. To explore the participants’ perspectives on using the monitor, the qualitative research interview will be supplemented with the System Usability Scale (SUS) [42] to gather additional information regarding the usability of the system.

Interviews and surveys will be conducted after participants have used the monitor for at least 2 months, allowing them to gain a more realistic understanding of the long-term use.

Data collected during the interviews will be analyzed using the thematic analysis approach developed by Liamputtong [43] and Braun and Clarke [44]. The SUS score will be calculated in accordance with the guidelines presented by Lewis and Sauro [45]. The scores will be analyzed descriptively by using statistical tools in Excel (Microsoft 365 MSO; version 2406, build 16.0.17726.20222).

### Statistical Analysis

Overall, the data analysis will include descriptive statistics and logistic regression. Descriptive statistics will be used to calculate mean, SD, and variance for RR, HR, and the time spent in different sleep stages. Logistic regression is particularly relevant when working with binary outcomes to calculate the probability of an event occurring based on one or more independent variables. Since this study investigates whether changes in physiological parameters occur in the nights preceding an exacerbation, logistic regression is an appropriate method for analysis. Logistic regression will be used to calculate the probability of developing an exacerbation based on the descriptives derived from RR, HR, and sleep stages as independent variables. Odds ratios based on logistic regression and the *F* statistic (*P*<.05) will determine whether each descriptive is independently associated with developing an exacerbation. Furthermore, correlations between the descriptives will be examined.

### Sample Size

A sample size of 40 participants will provide 90% power to demonstrate a significant correlation coefficient of 0.5 between the number of exacerbations and extremes or variations in RR, HR, and sleep stages. Considering a presumed dropout rate of 25%, based on previous findings in a study among people affiliated with TCN (ClinicalTrials.gov NCT05218525), 50 participants need to be recruited in this study.

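### At the stated 25% dropout, 50 recruits leave 37 to 38 completers, not the 40 behind the power statement; the effect on power is small

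*Protocol article*

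**What the plan says.** The Sample Size section of the protocol article makes two linked statements.

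- The power statement: "A sample size of 40 participants will provide 90% power". The target effect is a correlation of 0.5 linking the exacerbation count to unusual values or variability in the monitored signals.
- The allowance for losses: "Considering a presumed dropout rate of 25" per cent, from which it concludes that "50 participants need to be recruited in this study". The 25% is attributed to earlier findings among people affiliated with the same telemedicine service.

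The target of 50 is repeated in the Abstract (Methods) and under Recruitment. The section gives no inflation formula, significance level or sidedness. A threshold of 0.05 appears under Statistical Analysis, but there it belongs to the logistic regression. The article describes no replacement of dropouts and no lower dropout rate.

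**The concern.** The order of the two statements shows what each number is for: 40 is the number to be analysed, and 50 is the number to enrol so that 40 remain. A dropout rate is a share of those enrolled, so the enrolment figure comes from dividing 40 by the proportion retained. Fifty does not satisfy that at 25%.

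What is at stake is whether the recruitment target delivers the sample on which the power claim rests. The protocol takes its 25% from data in its own setting, so on its own evidence fewer than 40 completers is the expected result and not a pessimistic scenario. Whether this matters in practice depends on how much power is lost between 40 and the expected number, and that has to be calculated.

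**Working it through.** **Inputs from the Sample Size section:** 40 participants for analysis, 90% power, correlation 0.5, dropout 25%, 50 to recruit.

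**Assumption:** two-sided alpha of 0.05, because the section states neither level nor sidedness.

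**Step 1. Reproduce the 40.** With Fisher's z transformation, n = ((z_alpha + z_power)/atanh(r))^2 + 3.

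- Two-sided 0.05: ((1.960 + 1.282)/0.549)^2 + 3 = 37.8, so 38. This is within two participants of the stated 40.
- One-sided 0.05: 31.4, so 32. This does not reproduce 40.

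The two-sided reading is therefore the one that fits, and 40 is about two more than 90% power requires.

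**Step 2. Try to reproduce the 50.**

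- Dividing by the proportion retained: 40/(1 - 0.25) = 53.3, so 54. This does not match.
- Multiplying by one plus the dropout rate: 40 x 1.25 = 50. This matches exactly.

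**Step 3. What 50 recruits deliver.**

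- Completers at 25% dropout: 50 x 0.75 = 37.5, so 37 to 38, which is 2 to 3 short of 40.
- Dropout at which 50 recruits keep 40: 1 - 40/50 = 20%.

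**Step 4. Power for r = 0.5 at the expected number**, by three methods. Fisher z uses power = Phi(atanh(0.5) x sqrt(n - 3) - 1.960). The second method adds the usual bias correction r/(2(n - 1)) and takes the critical value from the t distribution. The third simulates the t test on bivariate normal data (200,000 samples for each n).

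| Completers | Fisher z | Bias-corrected | Simulated t test |
|---|---|---|---|
| 37 | 89.3% | 90.0% | 90.1% |
| 38 | 90.1% | 90.8% | 90.9% |
| 40 | 91.6% | 92.2% | 92.3% |

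The shortfall costs about 1.4 to 2.3 percentage points relative to 40 completers. Only the uncorrected Fisher approximation at n = 37 falls visibly below 90%.

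**The case against.** The strongest defence is that nothing of substance is lost. The 40 was slightly generous, since 38 is enough for 90% power, and that slack roughly absorbs the missing completers. Every method gives at least 90% at 38, and two of the three give 90% at 37. This stands, and it limits the weight of the point. It does not make the text correct: the section names 40 as its basis, and even a requirement of 38 would need 38/0.75 = 50.7, so 51 recruits.

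A second defence is to read the 25% as extra recruitment on top of 40, that is, 10 lost for every 40 kept. That describes a dropout rate of 10/50 = 20%, not the 25% stated.

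Some stronger readings are tempting, and the document does not support them:

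- **That the study is underpowered, or that the 90% claim fails.** A reader might infer this from the shortfall or from the 89.3% alone. That value comes from the least favourable approximation at the lower of two roundings.
- **That a multiplication by 1.25 is established as the cause.** It yields exactly 50 and is a plausible slip, but the article shows no formula, so it remains an inference. The inconsistency does not depend on it.
- **That 54 must be recruited.** That number is needed only to keep 40 completers. About 90% power does not require it.

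**Conclusion.** The point holds as an internal inconsistency in the sample size justification, and it is minor. At the protocol's own 25% dropout, 50 recruits give 37 to 38 completers and not 40; keeping 40 would need 54. This follows from the printed figures alone, and nothing elsewhere in the article reconciles them.

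Power for a correlation of 0.5 remains about 90%. That conclusion rests on a two-sided alpha of 0.05, on a single correlation tested with approximately normal data, and on 25% being the actual loss. What is lost is the small margin above 90% that 40 completers would have given.

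**What to change.** Restate the Sample Size section so that its figures agree: 50 recruited, with the 25% dropout seen in the earlier study, is expected to give 37 to 38 completers, which provides about 90% power for a single correlation of 0.5 at the stated alpha and sidedness (two-sided 0.05, if that is what was used).

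Keep the 25%. Relabelling it as 20% would make the arithmetic close, but it would set aside a rate that the protocol draws from its own setting without any data to replace it.

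The cost is one or two sentences and no additional participants. If the sponsor prefers to keep 40 completers, the target becomes 54. That is four more participants and a changed recruitment target, and Ethical Considerations says the protocol is not modified without new committee approval. The power figures give little reason to choose that route. The article reports 12 participants recruited so far, so the correction can be made before most of the sample is enrolled.

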### Ethical Considerations

The study has been approved by the Regional Ethical Committee for Medical Research in the North Denmark Region (N-20230072). The study will be performed in accordance with the tenets of Helsinki Declaration [31] and the principles of Good Clinical Practice. Written consent will be obtained from each participant after detailed verbal and written information about the study has been given and will be obtained before inclusion in the study [31]. Data will be anonymized and stored securely in compliance with the Danish Data Protection Rules [32]. The protocol will not be modified unless a new approval from the Regional Ethical Committee is obtained. The participants will not be provided with any compensation for their participation. There are no expected risks associated with participation in the trial. There is no increased risk of exacerbations, as the participants are not exposed to any interventions that could contribute to the development of exacerbations in COPD.

## Results

The study received final approval from the Regional Ethical Committee for Medical Research in the North Denmark Region on April 10, 2024 (N-20230072). In April 2024, the first participant information letter was sent by mail to the initial potential participants. The first participant was recruited in May 2024. A total of 12 participants have been recruited so far. Six out of 12 participants have been completed. These participants have also participated in qualitative research interviews at the end. The delivery of the remaining monitors has been delayed and is expected to be underway in March and April 2025. The remaining participants will be recruited once the delayed monitors are received. Data collection will begin as participants are recruited. The first participant completed the data collection stage at the beginning of October 2024 and the last participant is expected to complete this stage by September 2025.

## Discussion

### Anticipated Findings

The main finding of this study is presumed to be a new way to detect COPD exacerbations using contactless sleep monitoring. The study aims to provide knowledge regarding the possibility of detecting COPD exacerbations through frequent measurements of RR, HR, and sleep stages collected by using a contactless monitor during sleep. If the study proves that exacerbations can be detected by contactless measurements, the results have the potential to improve the ability to predict exacerbations in the future. Predicting exacerbations enables the possibility of initiating early treatment, which is expected to reduce hospitalizations and increase the quality of life among people with COPD.

Additionally, the study is also expected to provide knowledge regarding the experience of using the monitor more permanently. This is considered valuable knowledge about the potential of the monitor, as users’ experience and acceptance are important to consider when developing and implementing new technologies [46,47].

An expected strength of this study is the high frequency of measurements conducted over an extended time period. To our knowledge, no previous studies have monitored RR by a contactless monitor with a high frequency of measurements over an extended time period in people with COPD. However, continuous data collection can be crucial in this study because missing data from the nights preceding an exacerbation can reduce the ability to detect exacerbations, as symptoms primarily change a few days prior to onset [48]. While the recommendation to turn the monitor on/off throughout the entire project period is expected to meet the participants’ needs regarding privacy in the bedroom, this recommendation can also increase the risk of missing data. Therefore, it is important to be aware of missing data throughout the study period.

Another expected strength is that the measurements are conducted during sleep without physically touching the participants. This is expected to eliminate the discomfort associated with wearable equipment. Moreover, conducting measurements during sleep reduces the risk of data being influenced by factors like physical activity, which can be challenging to control when people perform the measurements at home during the day on their own. Øverst på formularen

This study may be limited by the risk of observing too few exacerbations during the project period. To address this, most participants will collect data during the winter, when exacerbations are more frequent. However, participants will also collect data at different times of the year, and thus across different seasons, which will help increase the generalizability of the results. Additionally, to mitigate this potential limitation, exacerbations of varying severities will be included to increase the likelihood of capturing exacerbations. This approach was also chosen because it is of interest to examine whether it is possible to detect changes or patterns in the days preceding different severities of exacerbations. The study has the potential to improve the ability to detect COPD exacerbations and thereby initiate early treatment to reduce hospitalization.

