**Objective:**

The aim of this observational study is to investigate whether contactless measurement of RR, HR, and sleep stages can be used to detect exacerbations in people with COPD.

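### The objective is to detect exacerbations, but the stated analyses can show only association, and a significant association is compatible with poor detection

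*Protocol article*

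**What the plan says.** The Objective in the Abstract is to "investigate whether contactless measurement of RR, HR, and sleep stages can be used to detect exacerbations in people with COPD". The Introduction repeats detection as both objective and hypothesis. Anticipated Findings goes further: "The main finding of this study is presumed to be a new way to detect COPD exacerbations using contactless sleep monitoring". It then continues "If the study proves that exacerbations can be detected by contactless measurements, the results have the potential to improve the ability to predict exacerbations", with the sentence ending on a reference to the future, and links this to earlier treatment and fewer hospitalizations.

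Statistical Analysis gives the inferential rule. It starts "Odds ratios based on logistic regression and the *F* statistic (*P*<.05" and says that these "will determine whether each descriptive is independently associated with developing an exacerbation". The same section says: "Logistic regression will be used to calculate the probability of developing an exacerbation". It attaches no alert threshold, accuracy measure or minimum performance to that probability.

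Sample Size rests on a different quantity: "A sample size of 40 participants will provide 90% power to demonstrate a significant correlation coefficient of 0.5". This correlation is between the number of exacerbations and extremes or variations in the signals. The Methods part of the Abstract also plans this correlation, together with a descriptive search for extremes or variations in the nights before an exacerbation.

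**The concern.** Detection is a statement about alerts: how often an exacerbation is preceded by one, and how often one is raised with no exacerbation to follow. An odds ratio compares the average signal between groups. It can differ convincingly from 1 while the two distributions overlap almost completely. The correlation with the number of exacerbations is a between-person quantity, so it cannot show that a change in the signal precedes an event.

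The article therefore states a claim of one kind and analyses of another. If an odds ratio turns out significant, a reader of Anticipated Findings could take the detection question as answered, and the article places earlier treatment and fewer hospitalizations downstream of that answer. If the signal discriminates poorly, nothing in the stated analyses would reveal it.

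**Working it through.** **The plan's own figure.** Inputs from Sample Size: r = 0.5, power 90%. Alpha is taken as two-sided 0.05; the article gives P<.05 without sidedness. By Fisher's z, n = ((1.960 + 1.282)/atanh(0.5))² + 3 = (3.242/0.549)² + 3 = 37.8, so 38. At n = 40 the power is 91.6%. The stated 40 is reproduced closely. It is a sample size for showing a correlation and carries no information on detection accuracy.

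**From odds ratio to discrimination.** Assume one descriptive, normally distributed with equal variance in the event and non-event groups. With the odds ratio (OR) expressed per SD:

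- shift between groups in SD: d = ln(OR)
- AUC = Φ(d/√2)
- sensitivity at 90% specificity = 1 − Φ(1.2816 − d)

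| OR per SD | d | AUC | Sensitivity at 90% specificity |
|---|---|---|---|
| 1.5 | 0.405 | Φ(0.287) = 0.613 | 1 − Φ(0.876) = 19% |
| 2.0 | 0.693 | Φ(0.490) = 0.688 | 1 − Φ(0.588) = 28% |

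The conversion does not use the sample size or the unit of analysis, so it holds for nights and for participants alike. If the unit is the night, 90% specificity over about 120 nights (4 months) means roughly 0.10 × 120 = 12 false-alarm nights per participant.

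**Can signals this weak reach P<.05?** The article gives neither the number of exacerbations nor the length of the pre-exacerbation window, so this step rests on assumed ranges. The shift that just reaches two-sided P = .05 is d = 1.96 × √(1/n1 + 1/n0), where n1 and n0 are the numbers of event and non-event units.

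- *Participant as unit:* 40 participants, 10 to 20 of them with an exacerbation. With 10, d = 1.96 × √(1/10 + 1/30) = 0.72; with 20, d = 1.96 × √(1/20 + 1/20) = 0.62. The just-significant OR is 1.86 to 2.05, AUC 0.67 to 0.69, sensitivity 25% to 29%.
- *Night as unit, nights treated as independent:* with 20 exacerbations and 3-night windows, n1 = 60 and n0 = 40 × 120 − 60 = 4740. Then d = 0.255, OR 1.29, AUC 0.57, sensitivity 15%. Over 10 to 60 exacerbations and windows of 1 to 7 nights, OR is 1.11 to 1.86, AUC 0.53 to 0.67, sensitivity 12% to 25%.
- *Night as unit, nights within an event adding little independent information:* at an assumed 1 exacerbation per year, 40 × 4/12 gives about 13 events, and the just-significant OR is about exp(1.96/√13) = 1.7.

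Under each of these assumptions, a descriptive that just meets the stated criterion has an AUC below 0.70 and, at 90% specificity, misses at least 70% of the units it should flag.

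**The case against.** The strongest reply is that Statistical Analysis ties P<.05 to one conclusion only, independent association. A reader might infer that the plan commits the study to declaring detection whenever an odds ratio is significant. No section says so, and that reading is not supported. Much of the wording is exploratory: Study Setting speaks of retrospectively looking for changes, the Abstract's Conclusions are cautious, and the sentence in Anticipated Findings is conditional. This stands. It does not remove the mismatch, because Anticipated Findings still presumes a new way to detect as the main finding, and none of the stated analyses measures that.

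Three other stronger readings also go too far.

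- *The odds ratio is the only criterion.* The correlation and the descriptive analyses are planned too, although they do not measure detection either.
- *Thousands of nights would make trivial effects significant.* The article states no unit of analysis, and the lowest thresholds above require independent nights. With about 13 events and strong clustering, an odds ratio of 1.5 would not reach significance.
- *The model would be judged on the data used to fit it.* The article is silent on validation, so this cannot be attributed to it.

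A condensed article may also leave accuracy measures to a fuller plan that is not shown. Their absence is therefore not the point here; the point is that the stated claim and the stated analyses do not match. Finally, the illustration treats one descriptive and, at night level, gives sensitivity per night. A model with several descriptives may discriminate better, which is a reason to measure it.

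**Conclusion.** The concern holds as a mismatch between claim and analysis. The objective and presumed main finding are detection; the odds ratios and the correlation can establish association only. An odds ratio of 1.5 to 2 per SD is compatible with an AUC of 0.61 to 0.69 and with 19% to 28% sensitivity at 90% specificity. Those figures rest on one descriptive, an equal-variance normal model and a specificity chosen for illustration. Event counts and windows enter only the check on which effects can reach significance, and they are assumptions. None of this predicts how the device will perform, and it does not show that the study will draw the wrong conclusion. It shows that meeting the stated criterion would leave the study's own question open. The data being collected can address that question, so this should be settled before the analysis.

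**What to change.** In Statistical Analysis, add measures of discrimination for the logistic model's predicted probability, from the same data:

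- AUC with a bootstrap interval that resamples participants
- sensitivity per exacerbation at a prespecified false-alarm rate
- both estimated with participants held out, for example leave-one-participant-out

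In Anticipated Findings, state that a significant odds ratio or correlation alone supports association, not detection.

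The cost is a little more analysis and no new data. The pre-exacerbation window and the alert rule have to be fixed beforehand. Ethical Considerations makes protocol modifications subject to new committee approval, so the team should check whether this addition counts as one. Intervals will be wide if exacerbations are few, a risk the article itself acknowledges. The measures should therefore be reported as estimates with their uncertainty rather than as a pass or fail test. With 12 participants recruited and 6 completed at the time of the article, the choice can still be made before the data are analysed.

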### Dissemination Plans

The results are expected to be published in international scientific journals. All results will be reported anonymously. The results will be published irrespective of whether they are positive, negative, or inconclusive. The authorship will be admitted to persons who have participated to the design, interpretation, conduct, and reporting of the trial. The results will also be communicated to participants who have indicated that they wish to be informed.

## Abbreviations

AAU: Aalborg University
CAT: COPD Assessment Test
COPD: Chronic obstructive pulmonary disease
DS-TOFHLA: Danish Short Test of Functional Health Literacy in Adults
HLS-EU-Q16: The European Health Literacy Survey Questionnaire
HR: Heart rate
MRC: Medical Research Council dyspnea score
QoL: Quality of life
RR: Respiration rate
TCN: TeleCare Nord
